## Adverse events

We will report the numbers and frequencies (%) of adverse events. Point estimates and 95% CIs will be reported, and p-values will be calculated using chi-square test.

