**First exclusion criteria (Preoperative exclusion criteria)**
1) Combined resection of liver, pancreas, colon (D1 resection or over) or/and paraaortic lymph node
2) Remnant gastric cancer
3) Diagnosis of double cancer
4) Allergic to Isocalclear (e.g. milk allergy)
5) Have advanced renal dysfunction (eGFR < 30mL/min/1.73m2)
6) Treated with insulin or poorly controlled diabetes mellitus.
7) Have organ dysfunction requiring strict restriction of drinking water.
8) Have psychiatric disorders or psychiatric symptoms that interfere with daily life
9) Participants judged otherwise unsuitable for participation by the investigators.

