### Criteria for discontinuing or modifying allocated interventions {11b}{18b(ii)-p}

The assessments, including HRQoL questionnaires, will be continued unless the participants withdraw consent for assessments. The following criteria will be used to discontinue the intervention:The participant requests discontinuation of the explanatory treatment.The participant cannot continue the explanatory treatment due to adverse events.The patient is found to be ineligible after initiation of treatment.The patient stops coming to the hospital due to relocation, etc.The patient dies.The study investigator determines that it is not appropriate to continue the explanatory treatment for any other reasons.

Unless the participant wishes to have his/her data destroyed or excluded, his/her already collected data will be retained and analyzed.

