## Sensitivity analyses

We will perform sensitivity analyses using a full analysis set (FAS) and a per protocol set (PPS). The FAS analysis will exclude participants who never ingest the ONS in the ONS group and those who are later found not to meet the eligibility criteria from the population for the ITT analysis. The population for the PPS analysis will comprise participants who ingested an average of ≥ 200 ml of the ONS per day.

We will also perform sensitivity analyses using a generalized linear mixed model with repeated measures analysis to estimate the mean difference in the change of the percentage of BWL.

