### Methods in analysis to handle protocol non-adherence and any statistical methods to handle missing data {20c} {20c-p}

All analyses will be on an intention-to-treat (ITT) basis. Randomized patients will be included and will be analyzed according to their allocated group regardless of what postoperative management they received. We will exclude the patients who have no available data and with protocol violations, such as patients who are later found not to meet the eligibility criteria.

We will document the amount of and reasons for missing data, if possible, between the ONS and control group. In case of dropout, we will describe the timing of dropout and, if possible, the reason.

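### The exclusion of late-found ineligible patients is worded for all analyses, so read literally it reaches the adverse-event comparison and conflicts with two other sections

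*Protocol article*

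**What the plan says.** All references are to the protocol article.

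- **Adverse events:** "We will report the numbers and frequencies (%) of adverse events". Point estimates, 95% confidence intervals and chi-square p-values follow. No population is named. Adverse events are item 6 of the secondary outcomes.
- **Methods in analysis to handle protocol non-adherence {20c}:** "All analyses will be on an intention-to-treat (ITT) basis". The next sentence reads "Randomized patients will be included and will be analyzed according to their allocated group regardless of what postoperative management they received". The one after it excludes patients without data and those "with protocol violations, such as patients who are later found not to meet the eligibility criteria". Nothing limits this to efficacy.
- **Criteria for discontinuing or modifying allocated interventions {11b}:** one reason to stop the intervention is "The patient is found to be ineligible after initiation of treatment". The section ends by saying that data already collected are kept and analysed unless the participant wants them destroyed or excluded.
- **Sensitivity analyses:** the full analysis set is formed by removing ONS patients who never took the product and "those who are later found not to meet the eligibility criteria from the population for the ITT analysis".
- **Table 1:** the preoperative exclusions include allergy to the product (milk allergy is the example), eGFR below 30, "Treated with insulin or poorly controlled diabetes mellitus", and organ dysfunction requiring strict fluid restriction. Only the allergy criterion is repeated at secondary enrolment, when patients are randomised.

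**The concern.** For efficacy, removing late-found ineligible patients is a familiar if debatable choice. For harms it works against the purpose of the table. Several exclusion criteria look like safety screens for this drink, and the first names the product. A patient who meets one of them, is randomised to ONS, takes the product and has an event belongs in the adverse-event comparison. Under the all-analyses rule as worded, that patient is removed.

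Allergy is the sharpest case. The reaction may be what shows that the patient was ineligible, so the outcome itself can trigger the exclusion. The rule is worded for both arms, but this route operates mainly in the ONS arm, which is assigned the product. The effect would be to tilt the comparison towards safety.

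The class of excluded violations is also left open, because late-found ineligibility is given only as an example. Those applying the rule will know the allocation, since physicians and statisticians are unblinded.

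**Working it through.** **Step 1. Does the exclusion reach adverse events?** Adverse events are a listed secondary outcome with a between-group test. The population rule covers all analyses, and no section exempts harms. On a literal reading, it does.

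**Step 2. Do the other sections agree?**

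| Section | Patient found ineligible after starting treatment |
|---|---|
| Non-adherence and missing data {20c} | Excluded, under a heading rule for all analyses |
| Discontinuing interventions {11b} | Stops the intervention; data already collected are kept and analysed |
| Sensitivity analyses | Removed from the ITT population to form the full analysis set, so still in ITT |

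These cannot all hold. If the first row governs, the ITT set has already lost these patients and removing them again for the full analysis set does nothing. If the second or third row governs, the exclusion sentence in the first is wrong. The article does not say which applies to adverse events.

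**Step 3. Arm size.** The plan's own figure reproduces. With a difference of 3 and an SD of 5.5, n per arm = 2 × (1.960 + 0.842)² × 5.5² / 3² = 52.8, so 53 per arm and 106 in total. Then 106 / 0.90 = 117.8, so 118 against a stated approximate 120. The illustrations below use only the planned 60 per arm.

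**Step 4. One reaction in the ONS arm (assumed).** Exact (Clopper-Pearson) limits:

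- Kept: 1/60 = 1.7%. Lower limit 1 − 0.975^(1/60) = 0.04%. The upper limit solves P(X ≤ 1) = 0.025 and is 8.9%.
- Removed: 0/59 = 0%. Upper limit 1 − 0.025^(1/59) = 6.1%.

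With two or three such patients, 2/60 (3.3%) becomes 0/58 and 3/60 (5.0%) becomes 0/57.

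**Step 5. Events in both arms (assumed).** Let 6/60 controls (10.0%) have an event. The ONS arm has 6 events plus k more, each in a patient later found ineligible. The test is an uncorrected chi-square.

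| k | ONS, all kept | p | ONS, k removed | p |
|---|---|---|---|---|
| 1 | 7/60 = 11.7% | 0.77 | 6/59 = 10.2% | 0.98 |
| 2 | 8/60 = 13.3% | 0.57 | 6/58 = 10.3% | 0.95 |
| 3 | 9/60 = 15.0% | 0.41 | 6/57 = 10.5% | 0.93 |
| 4 | 10/60 = 16.7% | 0.28 | 6/56 = 10.7% | 0.90 |

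At k = 4 the excess over control falls from 16.7 − 10.0 = 6.7 points to 10.7 − 10.0 = 0.7 points. No p-value crosses 0.05 either way. With k = 0 nothing changes.

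**The case against.** The strongest reply is that no section states that exposed, harmed patients are dropped from the safety result. The Adverse events section names no population, and an article may leave a separate safety set to the full protocol or analysis plan. That stands: the lack of a safety set is not the point here. The point is a general rule that is stated, reaches harms as worded, and contradicts two other sections.

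Four further limits also stand.

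- A reader might infer that the exclusion acts only in the ONS arm. It does not: the rule covers both arms. Renal dysfunction, insulin treatment or poorly controlled diabetes, and fluid restriction are pre-existing states that can come to light in either arm. Only allergy could plausibly be revealed by taking the product.
- Allergy is screened twice, and a reaction after starting also fits a separate discontinuation criterion, inability to continue because of adverse events. The article does not say that it would be reclassified as ineligibility.
- A reader might infer that harm is concealed. Under Adverse event reporting and harms, all serious adverse events are recorded in the EDC and shared with investigators. What is at risk is the between-group comparison, not the record.
- A reader might object to grouping by allocation because controls may take supplements. Supplements are allowed as part of usual care, so analysis by allocation validly compares the two strategies. It is not an error.

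The reply does not remove the contradiction. An analyst could follow the non-adherence section to the letter and leave an exposed, harmed patient out of the table.

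**Conclusion.** The concern holds in a limited form. The all-analyses exclusion, read literally, removes late-found ineligible patients from the adverse-event comparison, and it conflicts with the discontinuation and sensitivity-analysis sections. The documents do not support the flat statement that patients with these conditions are dropped from the safety result, because two sections point the other way.

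The size cannot be derived from the documents. They give no adverse-event rate and no count of late-found ineligible patients, and that count may be zero. Assuming 60 per arm, one to three affected ONS patients would be enough to turn a rate of 1.7% to 5.0% for a product-specific event into none observed. In the assumed scenarios with events in both arms, the estimated excess shrinks but no test result changes. The case for acting rests on a possible bias in the description of harms, which is cheap to prevent.

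**What to change.** 1. Reconcile the non-adherence, discontinuation and Sensitivity analyses sections, so that one statement says whether late-found ineligible patients belong to the ITT population.
2. Add to Adverse events, in words such as: adverse-event analyses include every randomised patient by allocated group, and no patient is removed because of ineligibility found later or a protocol violation.
3. ONS use by controls may be described alongside the table. It need not change the grouping, and moving such controls into the ONS column would break the randomised comparison.

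The cost is a few sentences. No new data are needed, and there is no added burden on patients or sites.

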### Interim analyses {21b}

We have omitted interim analysis due to issues related to multiple testing and insufficient statistical power. As serious adverse events are not anticipated, the omission is considered to be acceptable.

## Methods for additional analyses

### Subgroup analyses {20b}

We will perform the following subgroup analyses:Age (18–64 vs. 65–85)Sex (male vs. female)BMI (< 22 vs. ≥ 22)Surgical procedure (TG vs. non-TG)pStage (I vs. ≥ II)Postoperative AC (yes vs. no)

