## Background and rationale {6a}{6a-p}{7}{7-p}

Gastric cancer is the fifth most-common cause of cancer and third most-common cause of death worldwide [1]. Gastrectomy remains the main component of gastric cancer treatment. However, gastrectomy impairs the capacity of food retention and oral intake, which cause body weight loss (BWL) and decreased muscle mass [2, 3], muscle strength [4, 5] and health-related quality of life (HRQoL) [6]. Moreover, BWL after gastrectomy decreases patient adherence with adjuvant chemotherapy and worsens long-term prognosis [7–11]. Therefore, it is important to control the BWL after gastrectomy of patients with gastric cancer.

As recommended by the European Society of Clinical Nutrition and Metabolism (ESPEN) guidelines [12], oral nutritional supplements (ONS) have become an important part of postoperative nutritional management of patients with cancer. However, the outcomes of ONS after gastrectomy for patients with gastric cancer have been inconsistent [13–17]. A subgroup analysis of a systematic review also suggested no significant differences in weight loss between the ONS group and control group [18], although there was heterogeneity among studies in the type, amount, and content of ONS and duration of intervention.

It is believed that good ONS adherence is necessary to reduce BWL through intervention with ONS [16]. One of the barriers to maintaining patient adherence is the dislike of the flavor, texture, and viscosity of ONS [19]. It is commonly known that ONS formulations can lose their texture as a result of their complex nutrient content, and it is difficult to achieve a balance between comprehensive nutrition and the elements of ONS that promote patient adherence. In fact, it remains unclear if these comprehensive nutrients are actually essential for patients after gastrectomy who are not completely unable to take oral nutrition, although a previous study used a comprehensive supplement (i.e., trace elements, vitamins, n-3 fatty acid or fats) [13–17]. The main hypothesis for this study is that simple and smooth products that mainly include carbohydrates and proteins will reduce BWL of patients after gastrectomy compared to a regular diet.

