#### Intervention description {11a}{13}{13-p}{20c}

Patients assigned to the ONS group will receive two 200 ml (400 kcal) volumes of ready-to-drink and recloseable packaging products (ISOCAL® clear) per day added to their regular diet. Each 200-ml pack of ISOCAL® clear contains 200 kcal, 40 g of carbohydrate, 10 g of whey protein, no fat, 166 g of water, and 0 g of sodium. Patients will start the intervention as soon as possible after secondary enrollment, which is the timing of randomization and allocations and will be 5 to 7 days after gastrectomy. The intervention continues until 8 weeks after surgery, so the duration could vary between patients. Investigators will advise patients on how to consume the products in 1 day by presenting a short movie or study brochure.

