## Surgical procedure and postoperative management

The clinical and pathological stages of the malignancies were based on the Japanese Classification of Gastric Carcinoma [31]. Patients will undergo standard gastrectomy and lymph-node dissection according to the Japanese Gastric Cancer Treatment Guidelines, 6th edition [32]. Moreover, the standardization of the gastrectomy techniques has been established through the KEGG regular meetings. The surgeons choose the surgical approach (i.e., open or minimally invasive surgery) and reconstructive method according to their experience. For distal gastrectomy (DG), we will perform Billroth I (DG-BI), Billroth II (DG-BII), or Roux-en-Y reconstruction (DG-RY). For proximal gastrectomy (PG), we will perform esophagogastrostomy (PG-EG), double-tract method (PG-DT), or another reconstruction method. For total gastrectomy (TG), Roux-en-Y reconstruction (TG-RY) will be performed. When there is an esophageal invasion, transhiatal esophageal resection will be performed.

Patients will be allowed to drink water and ingest a solid diet according to the postoperative protocol of each institution. Patients will be discharged home when their primary-care physician approves. The intervention will be started before discharge in the ONS group. Patients with pathological stage II or III disease will receive adjuvant chemotherapy (AC) by S-1 with/without docetaxel or another regimen according to the Japanese Gastric Cancer Treatment Guidelines, 6th edition [32]. AC is usually started within 4–8 weeks [33, 34]. Because the duration until the primary outcome measurement time point is short and the study design is an RCT, the potential for bias due to AC is thought to be minimal.

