## Discussion

One of the important outcomes for patients with gastric cancer after gastrectomy is BWL. Previous studies investigating ONS for patients after gastrectomy have reported inconsistent results for this outcome [14–17, 28, 43]. This study will evaluate the effects of ONS with carbohydrate and protein on BWL, muscle strength, and HRQoL in the comparison with usual care. If this study shows better outcomes in the ONS group, it will provide evidence supporting the enhancement of postoperative daily activity in patients, better adherence to adjuvant chemotherapy, and better long-term prognosis.

Postoperative muscle strength and HRQoL after gastrectomy will be also examined. This simple ONS has 10 g of whey protein, including branched-chain amino acids, per 200 ml, which might help to prevent decreases in muscle strength. This potential beneficial outcome has been underappreciated [48], and this study will add novel evidence that might support this benefit.

Moreover, few studies have gathered information on energy intake from the regular diet [17]. We will collect the data on various nutrients in the regular diet, including on carbohydrates, protein, and fat, to assess the influence of ONS on the intake of energy and protein from the regular diet.

In previous studies, the common problem with ONS for patients with gastric cancer after surgery is poor adherence to ONS, which is reported to be approximately 45% to 68% of planned intake volume [14, 16, 43]. These studies [14–17, 28, 43] have used various types of ONS, and there is a possibility that these well-balanced oligomeric formulas or elemental diets could compromise the texture of ONS and lead to decreased adherence. If the adherence to ONS is higher than historical data [14, 16, 43] and some kinds of efficacy are shown compared with usual diet, patients with gastric cancer after gastrectomy can be offered practical alternatives with more acceptable texture.

To summarize, we have reported the protocol for a multicenter, open-label, parallel RCT that aims to evaluate the efficacy of ONS with simple nutritional ingredients for BWL following gastrectomy for gastric cancer. It is anticipated that the study findings will enhance our understanding of the benefits of ONS following gastrectomy and provide valuable insights into patient adherence and the effects on physical fitness and HRQoL. These insights could potentially transform postoperative care practices for patients with gastric cancer.

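### The subgroup by receipt of postoperative adjuvant chemotherapy is formed after randomisation, so comparisons within it can be biased

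*Protocol article*

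**What the plan says.** The Subgroup analyses section names six factors: age, sex, BMI, surgical procedure, pStage (I vs ≥II) and "Postoperative AC (yes vs. no"). The last carries no caveat and no separate status.

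Four other sections bear on it:

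- **Timing of allocation.** Intervention description ties the start of ONS to secondary enrolment, "which is the timing of randomization and allocations and will be 5 to 7 days after gastrectomy".
- **Timing and indication of AC.** Surgical procedure and postoperative management says "Patients with pathological stage II or III disease will receive adjuvant chemotherapy (AC") and "AC is usually started within 4–8 weeks". The same section concludes, citing the short follow-up and the randomised design, that "the potential for bias due to AC is thought to be minimal".
- **Weight loss, ONS and AC.** Background and rationale states that "BWL after gastrectomy decreases patient adherence with adjuvant chemotherapy and worsens long-term prognosis". Its main hypothesis is that a simple supplement "will reduce BWL of patients after gastrectomy compared to a regular diet". The Discussion says that better outcomes under ONS would support "better adherence to adjuvant chemotherapy, and better long-term prognosis".
- **Blinding.** The trial is open label. Patients, physicians and statisticians know the arm.

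**The concern.** A subgroup comparison keeps the protection of randomisation only if membership is fixed before allocation or cannot be affected by it. Having AC is not fixed by day 5 to 7. It is settled during the 8-week intervention, and the primary outcome, percentage body weight loss (%BWL), is measured at the end of that period. Early weight loss can come before the decision on AC, so the subgroup may be partly defined by the outcome process itself.

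If ONS lets some frailer patients start AC who would not have started under usual care, the ONS patients in AC-yes are on average frailer than the controls in AC-yes. AC-no is altered as well. An apparent difference in the ONS effect by AC could then be selection only. The trial's rationale invites readers to ask whether ONS works in patients having chemotherapy, so this subgroup is likely to be read causally.

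**Working it through.** **1. Order of events.** Randomisation is on postoperative day 5–7. AC usually starts within 4–8 weeks, and the primary outcome is measured at 8 weeks. The subgroup variable therefore arises after allocation and up to the time of the outcome.

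**2. Yardstick.** The Sample size section gives a difference of 3 points and an SD of 5.5. Per arm, n = 2 × (1.960 + 0.842)² × 5.5² / 3² ≈ 52.8, rounded up to 53, or 106 in total. This matches the stated figure. The protocol gives no figure for the AC subgroup, so its possible bias can only be illustrated.

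**3. Assumptions, none of them in the protocol.** AC is started only in pStage ≥II, by 70% of controls and by 80% or 85% of ONS patients. A patient starts if a standard normal recovery factor exceeds a threshold. Each SD of worse recovery adds b = 2 or 3 points of %BWL. ONS has no true effect on %BWL, and stage has none either.

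With φ the normal density at the threshold for proportion p: φ(70%) = 0.3477, φ(80%) = 0.2800, φ(85%) = 0.2332. Mean recovery among starters is φ/p. Among non-starters it is −φ/(1−p).

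**4. AC-yes.** Spurious ONS-minus-control difference = b × [φ(70%)/0.70 − φ(p)/p].

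- p = 80%: b × (0.4967 − 0.3500) = 0.29 (b = 2) or 0.44 (b = 3).
- p = 85%: b × (0.4967 − 0.2743) = 0.44 or 0.67.

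Positive values mean more weight loss under ONS.

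**5. AC-no.** This group also contains all pStage I patients. With s the share of pStage I, the mean excess loss in an arm is b × (1−s)φ(p) / [s + (1−s)(1−p)]. ONS minus control:

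| s | p = 80%, b = 2 / 3 | p = 85%, b = 2 / 3 |
|---|---|---|
| 30% | −0.06 / −0.10 | −0.15 / −0.22 |
| 50% | −0.07 / −0.10 | −0.13 / −0.19 |
| 70% | −0.04 / −0.06 | −0.08 / −0.11 |

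The range is −0.04 to −0.22, in favour of ONS. At s = 50% the false contrast between AC-yes and AC-no is 0.29 + 0.07 = 0.36 up to 0.67 + 0.19 = 0.86 points.

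**6. Check with a different model.** A simulation of 4 million patients per scenario used SD 5.5, half of patients in pStage ≥II, and a logistic model for AC.

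- True effect −3, with 60–80% having AC at average weight loss. If AC does not depend on weight loss or arm, both subgroups return about −3.0. If the log-odds of AC fall by 0.25, 0.5 or 1.0 per SD of weight loss, AC-yes gives about −2.96, about −2.86 and −2.5 to −2.7. AC-no stays at −3.0 to −3.1. The spurious interaction reaches about 0.5 points.
- No true effect, 70% having AC, ONS raising its log-odds by 0.5–1.0 and weight loss lowering it by 0.5–1.0 per SD. AC-yes shows +0.25 to +0.68, and AC-no shows −0.05 to −0.17.

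Both models agree on sign and order of size.

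**7. Noise.** With 60 per arm and half in pStage ≥II, AC-yes holds about 60 × 0.5 × 0.70 = 21 controls and 60 × 0.5 × 0.80 = 24 ONS patients. The standard error is 5.5 × √(1/21 + 1/24) ≈ 1.6 points.

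**The case against.** The best defence is that the protocol ties AC to pathology: patients with stage II or III disease are to have it. If receipt follows stage exactly, the subgroup is in effect determined by the resected specimen and no bias arises. That stands as a boundary case. But the subgroup then adds almost nothing to the pStage subgroup, and wherever it departs from stage, the departure can reflect recovery, weight, refusal or physician choice after allocation.

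A reader might infer that the protocol itself expects ONS to change who has AC. The text does not say so. Background and Discussion speak of adherence to AC, and the Discussion does so only on condition of a positive result. The step from adherence to starting is short and plausible, but it is an inference.

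A reader might also carry the distortion among pStage ≥II non-starters over to AC-no. Under the same assumptions that distortion is 0.48–1.19 points against ONS, but AC-no as listed includes the pStage I patients. The trial admits clinical stage I and stratifies on it, so some pStage I patients are to be expected. Including them makes the figure several times smaller and reverses its sign.

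It is also fair that the assumed bias is well below the standard error of about 1.6 points, and that this is one of six additional analyses on which neither the primary test nor the sample size depends. That limits the weight of the point. It does not make the comparison valid, because bias does not average out as noise does.

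The protocol's own remark that bias from AC is minimal does not meet the point. Short follow-up and randomisation protect the overall comparison of arms, not a comparison within groups formed afterwards.

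**Conclusion.** The point holds in a limited form. The AC subgroup is defined by an event after randomisation that recovery and weight loss, and so plausibly ONS, may influence, in an open-label trial. Comparisons within it can be biased. The documents do not support saying that they are biased, and they do not determine the size.

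Under the stated assumptions and no true effect, the spurious difference is about 0.3–0.7 points against ONS in AC-yes. It is about 0.04–0.2 points in favour of ONS in AC-no with 30–70% pStage I. The target difference is 3 points. The bias is zero if AC depends only on pStage. The primary intention-to-treat analysis is untouched. This is a preventable error of interpretation in an exploratory analysis and worth correcting.

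**What to change.** Delete the subgroup by AC received, or keep it with an explicit label that it is descriptive and does not estimate a causal effect. For the population in whom AC is indicated, rely on the pStage subgroup (I vs ≥II) already listed, since pStage is fixed by the specimen resected before randomisation. Its upper level is open-ended, while the treatment section names stages II and III only, so the match is close rather than exact. Report the number starting AC in each arm as an outcome. That shows directly whether ONS and AC start are related.

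The cost is one line of wording and the loss or relabelling of one exploratory subgroup. No data are lost, and the sample size does not change.
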